### 2.2. Study Design

NET-PD is a 2-year prospective single-center, double-blind, multi-arm, delayed-start, sham-controlled trial. The study is conducted in two stages—the pseudo-controlled and active-treatment stage—with each stage consisting of a 2-week intensive phase and a 12-week maintenance phase, for a total of 14 weeks. The intensive period involves daily or twice-daily iTBS (or pseudo-stimuli) per week, for a total of 10 or 20 sessions, and the maintenance period consists of 12 weeks of iTBS (or pseudo-stimuli) once or twice a day, 2 days a week, for a total of 24 sessions in the single-stimulation group or 48 in the double group. In stage 1 (pseudo-controlled stage), patients are randomly assigned to one of four intervention groups in a 1:1:1:1 ratio: early-start single iTBS group (A1), early-start double iTBS group (A2), delayed-start single iTBS group (S1), and delayed-start double iTBS group (S2). The early-start groups conduct active iTBS throughout, whereas the delayed-start groups use pseudo-stimuli in the first stage and start using iTBS in the second stage. The only difference between the single- and double-stimulation group is the number of sessions per day: once daily for the single group and twice daily for the double group. In stage 2 (active treatment stage), participants in A1 and A2 continue to receive the same iTBS protocol as the first stage, while those in S1 and S2 start to receive active iTBS. All patients are required to have a detailed follow-up clinical assessment and electrophysiology record at baseline, 2 weeks, 14 weeks, 16 weeks, and 28 weeks. MRI and peripheral blood are collected at baseline, 14 weeks, and 28 weeks (Figure 1, Table 1). Each patient will spend 7 months in this study and the total duration of the research will be approximately 2 years, from July 2022 (first in) to December 2024 (last out) (Figure 2).

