### 2.14. Baseline Assessments and Follow-Up Evaluations

After screening, all the eligible patients will undergo a comprehensive detailed assessment, including basic demographic, motor and non-motor symptoms, α-syn in the peripheral blood, and resting functional MRI, EEG, and EMG. All the physicians involved in assessment receive consistency training prior to the start of the trial to ensure the uniformity of the standard. Basic demographic information including gender, age, education, concomitant diseases, family history, medication usage, etc. is taken. All motor symptom assessments will be video-numbered and scored by two independent physicians. Various aspects of the patients’ clinical symptoms are measured using Unified Parkinson Disease Rating Scale (UPDRS), Berg Balance Scale (BBS), Hamilton Depression Scale (HAMD), Hamilton Anxiety Scale (HAMA), MMSE, Montreal Cognitive Assessment (MoCA), Pittsburgh sleep quality index (PSQI), 39-item PD Questionnaire (PDQ-39), 16-item odor identification test from Sniffin’ Sticks (SS-16), Scale for Outcomes in Parkinson’s disease for Autonomic Symptoms (SCOPA-AUT), and Wexner constipation scale. At the same time, we draw the patient’s peripheral blood for cytology, biochemistry, and coagulation tests and to detect α-syn in exosomes. After two intensive phases (week 2 and week 16), patients will receive a brief follow-up evaluation including the UPDRS, EMG acquisition and side effects. At midterm (week 14) and the endpoint of the experiment (week 28), the patients must complete the same detailed set of evaluations as the baseline.

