### 2.15. Outcome Measures

According to the results of previous large delayed-start design disease-modifying drug studies, the neuroprotective effect can be commonly reflected by the difference in the changes in the UPDRS score before and after treatment between groups [22,39]. In an NET-PD study, the primary outcome is the differences in changes in UPDRS scores in the four groups before and after the iTBS intervention. As a secondary outcome, we will evaluate the effects of iTBS treatment on clinical symptoms, motor symptoms such as gaiting and postural balance, and non-motor symptoms such as mood, cognition, olfaction, and sleeping condition in PD patients. As a neuro-modulation intervention study, EEG, EMG and MRI images can also be visualized to indicate the functional activity status of the brain. The safety of the treatment will be assessed using a self-administered side effect scale. Additionally, self-administered side effects scales will be used to assess iTBS safety.

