### 2.16. Study Hypothesis

Firstly, UPDRS scores are expected to be significantly lower in group A1 and A2 than in group S1 and S2 after stage 1, and the scores show a trend from low to high in groups A2, A1, S2, and S1 after stage 2. Next, the change in the slope of the weekly UPDRS scores will be compared among the 4 groups. We expect a slower rate of deterioration (i.e., increase in UPDRS scores) with the iTBS intervention than with the pseudo-stimulation group. The mean total UPDRS score deteriorates less from baseline to week 28 in the early-start groups than in the delayed-start groups. For the changes in slope of UPDRS scores between weeks 14 and 28, the early-start groups are expected to respond better than the delayed-start groups.

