### 2.17. Sample Size and Statistical Analysis

With reference to data from previous studies published in relevant journals, a total of 60 PD patients are proposed to be enrolled in this single center study. The sample size of this study was calculated based on the improvement in the UPDRS scale after 28 weeks of treatment and differences between groups. Calculations are performed using PASS (Power Analysis and Sample Size) 2008 software (UT, OH, USA), assuming a four-point reduction in the UPDRS at the end of treatment in A1, a five-point reduction in A2, a two-point reduction in S1, and a four-point reduction in S2, with a standard deviation of 2, a test level of 0.05, and a degree of certainty of 0.9 yielded for 13 subjects per group. Considering that the patient dropout rate may be about 10% [24,40], the final plan is to enroll n = 15 cases in each group for n = 60 cases in total. The minimum sample size required to meet the hypothesis of this clinical study is 60, and actual samples of 60 cases or more are in accordance with the clinical study design principles and statistical requirements.

Statistical analysis applies SPSS 20.0 for processing; MRI, EEG, and EMG data are processed on MATLAB platform (Math Works Inc., Natick, MA, USA). All statistics are performed using two-sided tests, and α = 0.05 is the cut-off point used to decide whether the hypothesis is statistically significant. Between-group comparisons of quantitative data will be performed using analysis of variance (ANOVA) or Wilcoxon rank sum test depending on the distribution of the data. A paired *t*-test or Wilcoxon signed-rank test will be used for comparison before and after treatment. Categorical data are tested by chi-square test or exact probability method (if the chi-square test is not applicable).

To compare the changes in UPDRS scores before and after the iTBS intervention at each time point, mainly comparing the differences in their means, two-way repeated-measures ANOVA was used to compare the main effects and the interaction effects between the two for different groups and follow-up points (baseline, week 14, week 28), and post hoc analysis was performed using the Bonferroni test to compare the differences between each follow-up point and baseline scores.

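### The UPDRS model in 2.17 uses only baseline, week 14 and week 28: the stage-2 slope then absorbs any step at iTBS start in the delayed arms, and the complete-case ANOVA discards partial data

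*Protocol article*

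**What the plan says.** Section 2.15 sets the endpoint: "the primary outcome is the differences in changes in UPDRS scores in the four groups before and after the iTBS intervention". Section 2.2 plans a "detailed follow-up clinical assessment and electrophysiology record at baseline, 2 weeks, 14 weeks, 16 weeks, and 28 weeks". Section 2.14 confirms that the short visits include the scale: "After two intensive phases (week 2 and week 16), patients will receive a brief follow-up evaluation including the UPDRS, EMG acquisition and side effects". The UPDRS row of Table 1 marks the same five occasions.

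Section 2.17 opens its UPDRS analysis with the aim "To compare the changes in UPDRS scores before and after the iTBS intervention at each time point". It then specifies that "two-way repeated-measures ANOVA was used to compare the main effects and the interaction effects" for "different groups and follow-up points (baseline, week 14, week 28"). No other model is named for UPDRS change, and no stated analysis uses weeks 2 or 16.

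Section 2.16 adds hypotheses about rates: "the change in the slope of the weekly UPDRS scores will be compared among the 4 groups". It also expects the early-start arms to do better than the delayed-start arms on the slope between weeks 14 and 28. Section 2.5 ends data collection for patients who discontinue.

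**The concern.** The five-visit schedule and the three-visit model do not match, and the aim of comparing changes at every time point sits awkwardly between them. This is not a detail left to a fuller document, because the article itself fixes the visit list and the type of model.

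Two consequences matter.

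- **Stage-2 slope.** S1 and S2 first receive active iTBS after week 14, and week 16 is their first UPDRS on it. If week 16 is left out, the slope between weeks 14 and 28 cannot separate a prompt response to starting treatment from the course that follows. A prompt response makes the delayed arms look as if they progress more slowly, which works against the direction that 2.16 expects.
- **Incomplete patients.** A classical repeated-measures ANOVA needs every listed visit from every patient. Anyone without a week-14 or week-28 score is removed, together with the scores already collected. Section 2.5 gives poor compliance and intolerable adverse events among its reasons for withdrawal, so those removed may differ from those who stay.

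**Working it through.** **1. The plan's own sample size.** Inputs from 2.17: UPDRS reductions of 4 (A1), 5 (A2), 2 (S1) and 4 (S2), SD 2, test level 0.05, power 0.9. A one-way ANOVA F test with four groups gives power 0.872 at 12 per group and 0.901 at 13, so 13 per group reproduces. With 10% dropout, 13 / 0.9 = 14.4, rounded up to 15 per group and 60 in total. This calculation rests on one change score at week 28, so the visit list does not affect it.

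**2. Visits collected and visits modelled.**

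| Week | 0 | 2 | 14 | 16 | 28 |
|---|---|---|---|---|---|
| UPDRS collected (2.2, 2.14, Table 1) | yes | yes | yes | yes | yes |
| In the 2.17 model | yes | no | yes | no | yes |

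**3. Stage-2 slope in a delayed arm.** Let b be the underlying change per week after week 14. Let s be an immediate improvement at iTBS start that is complete by week 16 (lower UPDRS is better). The documents give no value for s, so 1 to 3 points is an assumed range.

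- Slope over weeks 14-28: (14b - s) / 14 = b - s/14.
- Slope over weeks 16-28: 12b / 12 = b.

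| Assumed step s | Shift in week 14-28 slope | Shift in week 16-28 slope |
|---|---|---|
| 1 point | -1/14 = -0.07 per week | 0 |
| 2 points | -2/14 = -0.14 per week | 0 |
| 3 points | -3/14 = -0.21 per week | 0 |

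For scale, the sample-size assumptions imply early-minus-delayed differences at week 28 of 4 - 2 = 2 points (single stimulation) and 5 - 4 = 1 point (double stimulation). Steps of this range are of the same order. A1 and A2 also repeat an intensive phase at the start of stage 2, so in the between-arm comparison s stands for the extra step in the delayed arms.

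**4. Patients lost to a complete-case ANOVA.** At the planned 10%, 60 x 0.10 = 6 leave and 54 remain, against 4 x 13 = 52 required. The timing below assumes that dropout is spread evenly over 28 weeks. The 20% column is an assumed upper case.

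| | 10% dropout | 20% dropout |
|---|---|---|
| Leave before week 2 | 6 x 2/28 = 0.4 | 12 x 2/28 = 0.9 |
| Leave in weeks 2-14 (week-2 score only) | 6 x 12/28 = 2.6 | 12 x 12/28 = 5.1 |
| Leave in weeks 14-28 | 6 x 14/28 = 3.0 | 12 x 14/28 = 6.0 |
| Complete cases, three visits | 54 | 48 |
| Complete cases, five visits | 54 | 48 |
| At least one score at week 14 or 28 | 57.0 | 54.0 |
| At least one score at week 2, 14, 16 or 28 | 59.6 | 59.1 |

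The complete-case rows are equal because nobody who leaves has a week-28 score. Adding visits to the same ANOVA therefore recovers no one. A model that accepts incomplete records does.

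**The case against.** The three listed visits fit the design. Weeks 14 and 28 close the two stages, the hypotheses in 2.16 are framed around them, and the sample size rests on week 28. Weeks 2 and 16 are described as brief evaluations, and the parenthesis in 2.17 can be read as defining which time points are meant. The general between-group and paired tests in 2.17 could also be applied to the short visits. Missing-data handling is commonly left to an analysis plan, which is not shown.

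Much of this stands. A main model confined to stage-end visits is defensible for the week-28 question, and no model is labelled primary. The absence of a missing-data section is not the point. What does not stand is the slope. Section 2.16 promises a stage-2 slope comparison, the only stated model omits the visit needed to isolate the step, and no use of weeks 2 or 16 is stated. The choice of a complete-case model is likewise written into 2.17.

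Three stronger readings are tempting and should be set aside.

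- A reader might infer that the neuroprotection comparison fails. It does not, since early against delayed start at week 28 is estimable from the three visits.
- A reader might infer that week 2 alone would separate a symptomatic from a neuroprotective effect. It cannot. A symptomatic effect may also build up over 14 weeks of sessions, and the design relies mainly on whether the early-start advantage persists once all arms are treated.
- A reader might expect the extra visits to sharpen the week-28 estimate appreciably. With complete data and a separate mean for each group and visit, the week-28 change contrast is the simple difference in mean change, whatever other visits are modelled.

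**Conclusion.** The point holds in a limited form, and the analysis should be changed. As written, the stage-2 slope in S1 and S2 is contaminated by any prompt response to starting iTBS, by -0.07 to -0.21 points per week for an assumed step of 1 to 3 points. The shift is removed only to the extent that the step is complete by week 16.

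Separately, the type of model, not the visit list, costs about 6 of 60 patients at the planned dropout. About 5.6 of them (2.6 + 3.0) would have at least one post-baseline UPDRS if dropout is evenly spread. Power is not the main issue at 10%, with 54 complete cases against 52 needed. At an assumed 20% the complete cases would fall to 48. The stronger reasons to act are possible bias from excluding leavers and the waste of ratings already scheduled.

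**What to change.** In 2.17, replace the three-visit ANOVA with a likelihood-based mixed model fitted to all available UPDRS scores at baseline and weeks 2, 14, 16 and 28, with terms for group, visit and their interaction. Keep week 28 as the visit for the neuroprotection comparison. Report the early-minus-delayed difference at weeks 2, 14, 16 and 28. Estimate the stage-2 slope from week 16 to week 28, and align the slope hypothesis in 2.16 with it.

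The cost is wording, because every rating is already scheduled. Only two patients were enrolled when the article was written, so the change could have been specified well before results.

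There are three limits. The larger covariance matrix has more parameters to estimate with 60 patients. The week 16-28 slope covers 12 weeks instead of 14, so its standard error per week is larger by 14/12 = 1.17 if the difference in scores has the same SD. Finally, the mixed model still assumes that dropout is explained by the scores already observed.

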Neuroprotective or disease-modifying therapy can slow or even stop disease progression and prevent the onset of eventual functional disability [17], which is critical for PD patients. Neuroprotective therapy faces a few challenges, the most important of which is the limitation of experimental design. The traditional washout trial design suffers from the disadvantages involved in uncertain washout period and high patient dropout rate [18]. Delayed-start trial designs can largely solve this nuisance. This kind of design eliminates the symptomatic effect brought by treatment itself, enabling more precise monitoring of the “protective effect” results [19]. Moreover, delayed-start design does not need a washout period, which allows more patients to be treated and is more ethical; thus, patients may be more cooperative [20]. Several large cohort studies devoted to neuroprotection and disease modification have initially confirmed the reliability of the delayed-start trial design, and the current results found little disease-modifying effects for most drugs [21,22,23].

To validate the therapeutic effectiveness of iTBS, large randomized controlled studies with long-term follow-up are still needed to validate the results of current studies. Additionally, TMS has not been explored in any study for its neuroprotective effects in PD patients, nor was there definitive evidence of PD neuroprotection. Based on the research background and previous foundation above, NET-PD proposes to adopt a delayed-start randomized double-blind pseudo-stimulation controlled study design to perform multi-sequential M1-iTBS under individual MRI-navigation to explore the ameliorative and neuroprotective effect of long-term treatment with iTBS on PD patients, and to explore the potential mechanism of its therapeutic action by assessing the relationship between dynamic changes in multi-modal indexes and clinical symptoms. The investigators hope to provide a possible way to protect or even reverse neuronal loss in PD and delay the progression of motor disorders in PD.

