## 2. Methods/Design

### 2.1. Study Aims

The primary objective of NET-PD is to evaluate the neuroprotective effect of iTBS in PD patients. Secondly, clinical assessment and multi-modal markers are used to clarify the clinical improvement of motor symptoms and dynamic neuronal changes due to iTBS in PD patients, and to provide long-term follow-up evidence for the neuroprotective effect of iTBS. Meanwhile, by analyzing the dynamic changes before and after the treatment, we can explore the potential mechanisms of iTBS regulating brain and motor functions.

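### The UPDRS analysis ties no test to the week-28 early-versus-delayed hypothesis, and its group-by-visit interaction could let a purely symptomatic effect be read as neuroprotection

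*Protocol article*

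**What the plan says.** **Objective.** Section 2.1: "The primary objective of NET-PD is to evaluate the neuroprotective effect of iTBS in PD patients".

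**Design.** The Introduction gives the reason for a delayed start: "This kind of design eliminates the symptomatic effect brought by treatment itself". Section 2.2 says that "patients are randomly assigned to one of four intervention groups in a 1:1:1:1 ratio" (A1 and A2 early, S1 and S2 delayed; 1 = single, 2 = double stimulation). It adds that "the delayed-start groups use pseudo-stimuli in the first stage and start using iTBS in the second stage". Stage 1 ends at week 14 and stage 2 at week 28.

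**Outcome.** Section 2.15 says "the neuroprotective effect can be commonly reflected by the difference in the changes in the UPDRS score before and after treatment between groups", and then "the primary outcome is the differences in changes in UPDRS scores in the four groups before and after the iTBS intervention". It names no time point and no early-versus-delayed grouping.

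**Hypothesis.** Section 2.16 expects lower scores in the early arms after stage 1, less worsening from baseline to week 28 in the early arms, and a better week 14–28 slope in the early arms. It attaches no test to any of these.

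**Analysis.** Section 2.17: "two-way repeated-measures ANOVA was used to compare the main effects and the interaction effects between the two for different groups and follow-up points", with baseline, week 14 and week 28 as the visits. Then "post hoc analysis was performed using the Bonferroni test to compare the differences between each follow-up point and baseline scores". The section also has a general line giving ANOVA or a rank test for between-group comparisons of quantitative data. The sample size assumes UPDRS reductions of 4 (A1), 5 (A2), 2 (S1) and 4 (S2), SD 2, alpha 0.05 and power 0.9. This gives 13 per group, raised to 15 for 10% dropout.

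**The concern.** A delayed start separates protective from symptomatic benefit only through the comparison of early with delayed arms once all of them are on active treatment. Here that is week 28. At week 14 the early arms are active and the delayed arms are on sham, so a difference there is what any symptomatic treatment would produce.

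None of the tests named for UPDRS isolates week 28:

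- The interaction (6 df) pools every departure from parallel profiles, including the week-14 gap.
- The group main effect averages over baseline, week 14 and week 28, so it too is moved by the week-14 gap.
- The visit main effect and the comparisons with baseline show improvement over time, which a symptomatic treatment produces in all four arms by week 28.

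At stake is the trial's main conclusion. Because section 2.15 says that between-group differences in change reflect neuroprotection, a significant interaction could be reported that way when nothing protective has happened.

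**Working it through.** **1. The plan's own sample size.** One-way ANOVA of four groups, means 4, 5, 2, 4, SD 2. The grand mean is 3.75 and the squared deviations sum to 0.0625 + 1.5625 + 3.0625 + 0.0625 = 4.75. The noncentrality is n × 4.75 / 2², which is 15.44 at n = 13. Power is 87.2% at n = 12 and 90.1% at n = 13, so 13 reproduces. 13 / 0.9 = 14.4, rounded up to 15, so 60 reproduces. The stated 90% therefore belongs to a four-group omnibus test.

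**2. The interaction under a purely symptomatic effect.** Let each arm gain e points whenever it is on active iTBS, with no natural progression. Changes at (week 0, 14, 28) are (0, −e, −e) in A1 and A2 and (0, 0, −e) in S1 and S2. The true early-minus-delayed difference at week 28 is zero.

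- Interaction terms are e/6, −e/3, e/6 in each A arm and the opposite in each S arm. Their squares sum to e²/6 per arm, or 2e²/3 over four arms.
- Under compound symmetry, an SD of change of 2 means 2σ²(1−ρ) = 4, so the within-patient error variance σ²(1−ρ) is 2 whatever ρ is.
- The noncentrality is n × (2e²/3) / 2 = n e²/3, with 6 and 8(n−1) df.

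| e (points) | Noncentrality, n = 13 | Interaction significant, n = 13 | n = 15 |
|---|---|---|---|
| 1 | 4.33 | 27.4% | 31.8% |
| 1.5 | 9.75 | 59.7% | 67.6% |
| 2 | 17.33 | 87.5% | 92.6% |
| 3 | 39.00 | 99.9% | >99.9% |

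Simulations at ρ = 0.5 and 0.8 agree (at n = 13, about 27–28%, 59–60%, 87–90% and 99.8–99.9%). With no effect at all the interaction rejects in about 5%. The week-28 contrast of early with delayed arms rejects in about 5% in every one of these scenarios.

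**3. The other named tests, same setting.**

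- Group main effect: the averages over visits differ by 2e/3 − e/3 = e/3. For e = 2 and n = 15 it rejects in about 10% (ρ = 0.8) to 21% (ρ = 0.5).
- Week 28 against baseline, within arm, Bonferroni for three comparisons: for e = 2 and n = 13, significant in both early arms in 61–62% of trials, and at the same rate in both delayed arms. It does not discriminate.

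**4. The general four-group ANOVA, applied at week 28.** Suppose single stimulation gives 2 points, double gives 4, and early start gives nothing: means 2, 4, 2, 4. The squared deviations from 3 sum to 4, so the noncentrality is n × 4 / 4 = n. Power is 84.0% at n = 13 and 89.6% at n = 15.

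**5. The contrast that matches the hypothesis, under the plan's means.** (4 + 5)/2 − (2 + 4)/2 = 1.5 points. Its standard error is 2 × √(4 × 0.25/n) = 2/√n.

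- n = 13: SE 0.555, noncentrality 2.70, 48 df, power 75.5%.
- n = 15: SE 0.516, noncentrality 2.90, 56 df, power 81.5%.
- For 90%, the normal approximation gives 38 per pooled side, or 19 evaluable per group. The t distribution gives 89.7% at 19 and 91.2% at 20.

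**The case against.** **The hypothesis is stated.** Section 2.16 does name baseline to week 28, early against delayed, and section 2.17 has a general between-group ANOVA. A reader might infer that the plan never considers the week-28 comparison; the documents do not support that. What stands is that no test is tied to it, and that the general ANOVA, even if applied at week 28, responds to dose alone.

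**The interaction is not called the primary test.** This is correct. The sample size even reproduces as a one-way comparison of changes after 28 weeks. A reader might infer that a symptomatic effect would necessarily be reported as neuroprotection. The article does not say that a significant interaction alone decides the matter, so only *could* is justified. The percentages above are power to detect a real difference in profiles; they become false claims only through that reading.

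**The post hoc sentence is ambiguous.** It might mean comparing change from baseline between groups at each visit. Even so, it names neither the pooled early-versus-delayed contrast nor week 28 as decisive.

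**The outcome wording.** A reader might take before and after iTBS to mean weeks 14–28 in the delayed arms and weeks 0–28 in the early arms. That is strained, since sections 2.16 and 2.17 both measure change from baseline, and nothing here rests on it.

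**The article is condensed and an analysis plan may exist.** That would excuse silence. Here the model, the visits and the follow-up comparisons are stated, and they do not match the stated hypothesis.

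**The week-28 contrast is not proof either.** This stands. Its 5% rejection rate assumes full catch-up. A symptomatic benefit that grows with exposure (28 against 14 weeks active) would make it positive without neuroprotection.

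**Conclusion.** The concern holds as a mismatch between the stated hypothesis and the stated analysis. The named UPDRS tests can be strongly positive when the early-versus-delayed difference at week 28 is exactly zero: about 87% of trials for a 2-point symptomatic effect at 13 per arm and 93% at 15. Effects of that size are within what the plan assumes (reductions of 2 to 5 points). The percentages rest on the plan's SD of 2 taken as the SD of change, compound symmetry, no natural progression and full catch-up by week 28. The assumed correlation does not drive them. The sample-size arithmetic is right for the omnibus test, but that test does not answer the primary objective.

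**What to change.** In sections 2.15 and 2.17:

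1. Define the primary outcome as change in total UPDRS from week 0 to week 28 in every arm.
2. Make the primary test one pre-specified contrast at week 28, (A1 + A2)/2 minus (S1 + S2)/2, two-sided at 0.05.
3. Report the same contrast at week 14 as the sham-controlled symptomatic effect.
4. Keep the week 14–28 slope comparison of section 2.16 as supportive evidence on whether the arms converge.
5. Treat within-arm comparisons with baseline as descriptive.
6. State that a week-28 difference could also come from symptomatic benefit accumulating over longer exposure.

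**Cost.** No new visits or measurements. The power statement must change: about 75% at 13 per arm and 81% at 15 for the 1.5-point contrast. Restoring 90% would take 19 to 20 evaluable per group; dividing by 0.9 gives 22 to 23 enrolled per group, or 88 to 92 in total against 60 planned. If the sponsor keeps 60, it should state the lower power openly.
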